### Interviewer training and the management system

The DIMOSI fieldwork was conducted by a team consisting of sleep researchers, psychiatrists, research assistants, and nurses. A study manager based at Guangdong Mental Health Centre, Guangdong Provincial People’s Hospital (Guangdong Academy of Medical Sciences) oversaw the supervisors and their teams. Among the four experienced supervisors, two were PhD-level psychiatrists (with 17 and 13 years of clinical experience, respectively), one was a postdoctoral sleep researcher (with 5 years of clinical research experience), and one was an MA-level clinical mental health researcher (with 2 years of clinical research experience).

Each interviewer conducting clinical assessment for participants was required to hold at least a bachelor’s degree and 2 years of experiences in clinical research. Interviewers were also required to complete a 20-hour General Interviewer Training (GIT) course before working on any DIMOSI survey, which included text, video, and on-site observational learning. Potential interviewers were required to pass an interview test before being allowed to contact participants. They needed to successfully complete three independent interviews under the supervision of two professional DIMOSI interviewers and had to pass a stringent examination. Failure was defined as making 3 or more errors out of the 393 test items.

In the pilot phase, we invited two centres to participate in the platform testing, involving a total of 98 subjects throughout the research process. Based on the issues encountered during testing, we refined quality control details and optimized software functionality. To ensure the system meets the needs of both participants and researchers, ongoing monitoring of the platform’s acceptability and usability will be conducted, including monitoring the apps, assessment scheme, hardware measurement devices, e-CBTI platform, and web management platform. After the official start of the study, real-time monitoring of backend data was implemented and participants were contacted if data stream disruptions occurred from any device to determine whether issues were related to functionality or user experience. Researchers conduct weekly quality control assessments, and provide feedback to each centre.

Through monitoring of the collected data via the administrative interface, a data quality assessment is conducted using a data quality control checklist. The checklist covers aspects such as interview duration, interview logistics, physiological data quality, activity diary completion time, and the level of information completeness. Monitoring results are documented in a standardized data quality feedback form and provided as feedback to each centre. Figure 4 shows the administrative interface.

**Fig. 4 Fig4:**
[figure not shown]
Administrative interface of the DIMOSI digital platform

### Statistical analyses plan

#### Baseline descriptive analyses

The study will estimate descriptive statistics for demographic data, drop-out rates, and the number of participants using digital tools, ensuring no data loss or damage and maintaining data integrity throughout the research period. Multiple imputation will be applied to handle missing data if necessary.

#### Multimodal data integration

Questionnaire, EMA, wearable, and cognitive task data will be integrated using a unified preprocessing and clustering framework. Within each modality, features are selected to capture distinct aspects of insomnia-related functioning, such as mental disorders and symptoms, cognition, objective sleep parameters, and demographic characteristics. Variables with low variance or > 30% missingness will be excluded. To eliminate the influence of differing scales and units across features, continuous variables are standardized using Z-score normalization.

To address multicollinearity and redundant information, we construct a pairwise correlation matrix and visualized it with a heatmap to identify highly correlated feature pairs (|r| > 0.8). Two mainstream strategies will be considered: (1) Feature selection using Lasso regression with 10-fold cross-validation to retain the most informative variables while shrinking redundant coefficients to zero; and (2) Feature dimensionality reduction using principal component analysis (PCA), which transforms correlated variables into orthogonal principal components while preserving most of the data variance. After preliminary testing, PCA is selected as the final approach based on its superior performance in preserving global data structure and compatibility with K-means clustering’s independence assumptions. Components explaining > 85% of the cumulative variance will be retained for subsequent analyses.

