### Study population

To determine the subtypes of insomnia disorder and explore their predictive value for trajectory and intervention outcomes, an estimated 40–80 variables will be included in the statistical model. Based on an estimated events per variable (EPV) of 50 to ensure sufficient statistical power, a total of 4,000 participants are required at the baseline [28].

Participants aged 18–65 years with a lifetime history or current insomnia disorder will be recruited. Subjects will be included in the study if they meet the following inclusion criteria: a. Previously or currently meeting the diagnostic criteria for insomnia disorder in ICSD-3; b. Ability to read and understand Chinese, and use the devices required for the study; c. Ability to provide informed consent. The exclusion criteria are: a. Lifetime history of schizophrenia, intellectual disability, or severe physical illness; b. Pregnancy or lactation; c. current involvement in other clinical research projects.

As of June 2025, 33 study sites specializing in psychiatry, neurology, or sleep medicine have taken part in the current study. The principal research centre of the DIMOSI study is located at the Guangdong Mental Health Centre, Guangdong Provincial People’s Hospital (Guangdong Academy of Medical Sciences), Southern Medical University, Guangzhou, China. Additionally, 33 study sites across various regions of China have joined as collaborative institutes (Fig. 2).

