#### Subtyping procedures

The standardized features from each modality are concatenated into a single feature matrix, and variance normalization is applied to balance the contribution of different modalities in subsequent analyses [75, 76]. PCA was further applied for dimensionality reduction, followed by K-means clustering to identify distinct insomnia subtypes.

The optimal number of clusters (k) was determined using the elbow, silhouette, and Gap statistics. To assess clustering robustness, bootstrap resampling (1,000 iterations) and consensus clustering will be performed [77]. Cluster characteristics will be summarized using standardized centroid differences and key feature importance, providing interpretable profiles of each subtype. Sensitivity analyses will be conducted to compare equal-weight versus data-driven weighting schemes to evaluate the robustness of the clustering results. The defining features of each cluster are examined to understand the underlying pathophysiological mechanisms and clinical presentations.

Aggregated features obtained from Zhiyoumian and wearable devices as well as their changes from baseline, will be incorporated into the statistical analyses. Machine learning techniques will be applied to build predictive models evaluating the stability and clinical predictive value of these subtypes.

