## Results

In the current study, 127 researchers across study sites received consistent training in clinical interviews, the use of wearable devices, and other psychological assessments. We randomly selected 46 researchers to complete a reliability assessment for 8 clinical structural interviews. The Cochran’s Q values ranged from 29.2 to 43.0, with all p-values > 0.05, indicating a high consistency among interviewers.

From November 28, 2022, to June 30, 2025, approximately 5000 individuals with suspected insomnia disorder were screened. A total of 3134 participants were interviewed, of whom 2937 (93.7%) were recruited and 197 (6.3%) were excluded. Among those recruited, there are 1743 (59.3%) from outpatient clinics and 1194 (40.7%) from community settings. The most common reason for exclusion was psychotic symptoms resulting from other mental disorders, which led to the inability to complete the clinical interview. The recruitment procedure is shown in Fig. 3.

All participants met the ICSD-3 criteria for insomnia disorder, with a mean age of 37.3 ± 12.6 years and 1952 (66.5%) were females. At baseline, 2850 participants (97.1%) were suffering from current insomnia disorder as defined by the clinical interview based on ICSD-3. In terms of comorbidities, assessed by the structured clinical interviews administered via the Zhiyoumian-Researcher app, 505 participants (17.2%) had current depressive disorders, and 613 participants (20.9%) had current anxiety disorders. The mean score of the ISI was 15.5 ± 5.8, with a median (interquartile range) score of 16.0 (7.0). When comparing those from the community setting and clinic, we found that the participants from the clinic are significantly older than their counterparts. But there is no statistical difference in sex, comorbidities, and insomnia severity (Table 2).

**Table 2 Tab2:** Demographics, comorbidities, and insomnia severity in participants from community and clinic settings（*N* = 2937）

	Community(*n* = 1194)	Clinic（*n* = 1743）	*p*
Age, mean±SD	35.9±12.3	38.2±12.3	＜0.001
Gender Female, n(%)	780 (65.3%)	1172 (67.2%)	0.283
Comorbidities, n(%)	364 (30.5%)	484 (27.8%)	0.115
Depressive Disorder	212(17.8%)	293(16.8%)	0.518
Generalized Anxiety Disorder	270(22.6%)	343(19.7%)	0.058
Bipolar Disorder	39(3.3%)	48(2.8%)	0.439
Panic Disorder	15(1.3%)	25(1.4%)	0.748
Post-Traumatic Stress Disorder	25(2.1%)	45(2.6%)	0.460
ISI, mean±SD	15.7±5.84	15.3±5.79	0.101
ISI ≥ 8, n(%)	1104(92.5%)	1602(92.9%)	0.625

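### Features are scaled for units only and demographics are among the inputs, so age or sex can define a cluster, and no planned check tests whether it survives their removal

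*Protocol article*

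**What the plan says.** Under Multimodal data integration the purpose of standardisation is given as "To eliminate the influence of differing scales and units across features", and the method as "continuous variables are standardized using Z-score normalization". The domains from which features are drawn are listed there: "such as mental disorders and symptoms, cognition, objective sleep parameters, and demographic characteristics".

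Under Subtyping procedures, "The standardized features from each modality are concatenated into a single feature matrix", the variance of the modalities is balanced, and then "PCA was further applied for dimensionality reduction, followed by K-means clustering to identify distinct insomnia subtypes". The number of clusters k is chosen by elbow, silhouette and Gap. Robustness is assessed by 1,000 bootstrap resamples, consensus clustering and one named comparison: "Sensitivity analyses will be conducted to compare equal-weight versus data-driven weighting schemes". Clusters are profiled by their centroids and most important features, and these are to be read for mechanism and clinical presentation. Predictive models then assess the stability and prognostic value of the subtypes.

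Under Study population: "Participants aged 18–65 years with a lifetime history or current insomnia disorder will be recruited". Under Results, mean age is 37.3 years (SD 12.6) and 66.5% are female. The statistical control mentioned under Strengths and limitations concerns sleep medication. The community-clinic sensitivity analyses named there concern selection bias.

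**The concern.** A Z-score is a linear rescaling. It equalises units and leaves every correlation with age and sex as it was. No age- or sex-referenced scaling, residualisation or stratified clustering is described, so scaling over the whole cohort is the natural reading. If EEG sleep measures, rest-activity measures and reaction times share an age gradient, that gradient is common variance. PCA gathers it into a component, and K-means may split along it. Entering age or sex directly as a demographic feature adds to the same axis.

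At stake is the meaning of the main deliverable. A group that differs chiefly in age could be named an objective-sleep or cognitive subtype, and its later course reported as subtype prognosis. Bootstrap and consensus clustering do not protect against this, because they measure reproducibility and an age axis reproduces well.

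**Working it through.** **The plan's own figure.** The feature count comes from Study population: 40 to 80 variables at 50 events per variable, so 80 × 50 = 4,000. This reproduces and is not in dispute. The midpoint, (40 + 80)/2 = 60 features, is used below.

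**Assumed, because the documents do not give it.** The correlation r of m features with age, and the loading s of the remaining 60 − m features on one factor unrelated to age.

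**Why the answer varies.** If m features are related only through age, their leading eigenvalue is 1 + (m − 1)r². The competing factor has 1 + (60 − m − 1)s². For m = 15 and r = 0.2: 1 + 14 × 0.04 = 1.56. For m = 30 and r = 0.3: 1 + 29 × 0.09 = 3.61. A factor with s = 0.3 on 45 features has 1 + 44 × 0.09 = 4.96. With two clusters, K-means tends to split on the larger axis. With four, it can use both.

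**Simulation 1.** 4,000 people, age normal (37.3, SD 12.6) cut to 18–65, Z-score, PCA to 85% of variance, K-means, two data sets per setting, no true subtypes, no modality balancing. Selected settings:

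| m | r | s | eigenvalue, age | eigenvalue, other | age variance explained, k=2 | age gap, k=2 (years) | age variance explained, k=4 |
|---|---|---|---|---|---|---|---|
| 15 | 0.1 | 0 | 1.14 | – | 0.5% | 1.2 | 1.6% |
| 15 | 0.2 | 0 | 1.56 | – | 25% | 10.5 | 18.5% |
| 15 | 0.3 | 0.3 | 2.26 | 4.96 | 0% | 0.3 | 30% |
| 15 | 0.2 | 0.5 | 1.56 | 12.00 | 0% | 0.3 | 0.1% |
| 30 | 0.3 | 0 | 3.61 | – | 52% | 15.4 | 61% |
| 30 | 0.3 | 0.3 | 3.61 | 3.61 | 42% | 13.3 | 52% |
| 30 | 0.4 | 0.5 | 5.64 | 8.25 | 0.3% | 1.1 | 51% |

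After residualising on age and sex, clusters explained at most 0.1% of age variance, and the k=2 gap was about 0.3 years or less, in every setting.

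**Simulation 2.** n = 2,937, 60 features, questionnaires on one general and five specific factors, k fixed at 4, no true subtypes. With 20 objective or cognitive features correlated 0.2, 0.3 and 0.4 with age, cluster mean ages spread over 7, 16 and 20 years. With 12 such features they spread over 1, 2 and 12 years. After age was regressed out the spread was 1 year or less. The adjusted Rand index between the two partitions was 0.35 to 0.86.

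**Simulation 3, with the planned modality balancing.** As in simulation 2, with assumed loadings of 0.4 (general) and 0.5 (specific) for questionnaires, 0.4 on three specific factors for objective features, the two blocks given equal total variance, and three data sets per setting. At k=2 the gap was 0.6 to 1.1 years for r = 0.2 or 0.3, but 13.5 (12 features) and 14.1 (20 features) for r = 0.4. At k=4 it was 10.5 to 17.9 years across all six settings. The largest value was 21.6 years (20 features, r = 0.4, k=5). After age was regressed out, the gaps checked (k=2 and k=4) were at most 0.8 years.

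No simulation gave sex an effect on the features. The sex part rests on the same algebra, without a figure.

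**The case against.** The strongest reply is that listing demographic characteristics among the features is a choice. The authors may want age to help define subtypes, and age-linked presentation may be real heterogeneity in insomnia. That stands as a reason not to make residualisation the primary analysis. It does not remove the need to know which subtypes depend on age.

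A second reply is that the planned rules for k may not select the partition in question. In a no-subtype simulation with strong questionnaire factors and no modality balancing, Gap chose k=1 in all six settings. Silhouette peaked at k=2 (about 0.10 to 0.12), where ages differed by 0.1 to 0.7 years. Spreads of 10 to 19 years appeared only at k of 3 or more, with silhouette at most 0.08. This rightly limits the weight of any figure from a fixed k. It does not dispose of the point: real subtypes would support a larger k, and with balancing a large gap can appear at k=2.

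Third, this is a journal article and covariate handling may sit in a fuller plan. The article does, however, set out the preprocessing sequence, its purpose, the inputs and the robustness checks, and the point rests on those statements.

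Stronger readings that a reader might infer are not supported:
- That nothing planned would reveal an age-driven cluster. Centroid profiles could show that a cluster is older. They cannot show whether it survives adjustment.
- That ordinary ageing will be reported as a subtype. Every participant has lifetime or current insomnia disorder, no healthy comparison group is described, and no age correlations are given.
- That the age difference by setting ("we found that the participants from the clinic are significantly older than their counterparts") makes matters materially worse. It is 38.2 − 35.9 = 2.3 years, or 2.3/12.3 = 0.19 SD. A 16-year gap between clusters would imply a difference in clinic share of about 0.593 × 0.407 × 2.3/12.3² × 16 = 0.06, or 6 percentage points.

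**Conclusion.** The point holds as a possibility that the plan leaves untested. The scaling step keeps age and sex variation, demographics may enter directly, and no stated robustness check separates a reproducible age or sex axis from an insomnia subtype. Leaving the features unresidualised is not in itself an error, and nothing in the article is numerically wrong here.

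The size cannot be derived from the documents. Under assumed age correlations of 0.2 to 0.4, gaps in cluster mean age run from about 0 to over 20 years. The effect is negligible where age correlations are weak, or where a strong competing factor dominates and k is small. It is largest with many age-related features, modality balancing and a larger k. This is a low-cost improvement that limits what can be claimed about the primary outcome. It is not a flaw that invalidates the plan.

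**What to change.** Add one pre-specified sensitivity clustering:

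1. Keep age and sex out of the inputs. Residualising the other features alone would leave age in the matrix.
2. Replace each wearable, EEG and cognitive-task feature by its residual from a regression on age (linear and quadratic) and sex, then Z-score.
3. Run the same balancing, PCA and K-means, with k chosen by the same planned rules.
4. Report the adjusted Rand index against the planned partition, and the age and sex mix of every subtype.
5. Describe a subtype that does not persist as age- or sex-related, not as a distinct objective or cognitive insomnia subtype.

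The cost is one further run on data already collected, with no change to sample size or assessments. The downside is that heterogeneity genuinely tied to age is muted in the adjusted run, so both versions should be reported side by side.

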#### Subtyping procedures

The standardized features from each modality are concatenated into a single feature matrix, and variance normalization is applied to balance the contribution of different modalities in subsequent analyses [75, 76]. PCA was further applied for dimensionality reduction, followed by K-means clustering to identify distinct insomnia subtypes.

The optimal number of clusters (k) was determined using the elbow, silhouette, and Gap statistics. To assess clustering robustness, bootstrap resampling (1,000 iterations) and consensus clustering will be performed [77]. Cluster characteristics will be summarized using standardized centroid differences and key feature importance, providing interpretable profiles of each subtype. Sensitivity analyses will be conducted to compare equal-weight versus data-driven weighting schemes to evaluate the robustness of the clustering results. The defining features of each cluster are examined to understand the underlying pathophysiological mechanisms and clinical presentations.

Aggregated features obtained from Zhiyoumian and wearable devices as well as their changes from baseline, will be incorporated into the statistical analyses. Machine learning techniques will be applied to build predictive models evaluating the stability and clinical predictive value of these subtypes.

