The rapid advancement of digital technology over the last decade has revolutionized mental health care, providing new opportunities for the assessment and management of mental disorders [22–25]. Wearable devices, including smartphones and accelerometers (Axivity AX3), have emerged as tools to monitor sleep and circadian rhythm, capturing changes in physical activity, environment, and related mental status simultaneously [26, 27]. However, few assessment platforms have integrated subjective and objective measurements, for insomnia disorder. To systematically assess core features of insomnia disorder and its related characteristics, an integrated digital platform, called Zhiyoumian (知优眠 in Chinese, meaning “know and improve your sleep”) was established for this study, consisting of two apps and a website for comprehensive assessments.

The Digital Multi-modal Approaches to Subtyping Insomnia Disorder (DIMOSI) study (ChiCTR2200056425 in Chinese Clinical Trial Registry) is designed to address the critical gaps, including: (a)providing objective and continuous data to complement subjective reports, (b) capturing dynamic, real-world fluctuations rather than the single-night PSG assessment, and (c) simultaneously assessing multiple functional modalities to create a holistic profile. We hypothesize that the integration of multi-modal digital data, including clinical interview, self-report, ecological momentary assessment (EMA), data from wearable devices, and cognitive tasks, may capture the interaction between the behavioral, emotional, circadian, and cognitive systems that underlie insomnia heterogeneity, leading to a precise subtype system of insomnia disorder. The DIMOSI aims to achieve the following: (a)exploring the subtypes of insomnia disorder using comprehensive multi-modal assessment approaches, (b) validating the stability and predictive accuracy of the identified subtypes through a prospective study with follow-up assessments at 6 months and 12 months (c)determining the natural trajectories and related mental health outcomes of different subtypes of insomnia disorder. This fine-grained, data-driven subtyping study for insomnia disorder is anticipated to transcend unstable, symptom-based classifications and accelerate the development of clinical paradigm (Fig. 1).

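### The clustering sequence does not separate overall severity from symptom pattern, so under plausible inputs K-means can return mild-to-severe bands that the planned checks would not identify

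*Protocol article*

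**What the plan says.** The Abstract of the protocol article names identification of the subtypes as the primary outcome. The sequence that produces them is set out in Multimodal data integration and Subtyping procedures:

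- Scaling is per variable: "continuous variables are standardized using Z-score normalization".
- Modalities are then balanced: "variance normalization is applied to balance the contribution of different modalities in subsequent analyses".
- PCA is chosen over Lasso, and "Components explaining > 85% of the cumulative variance will be retained for subsequent analyses".
- The last step reads: "PCA was further applied for dimensionality reduction, followed by K-means clustering to identify distinct insomnia subtypes".

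The number of clusters comes from the elbow, silhouette and Gap criteria. Robustness is examined by 1,000 bootstrap resamples, by consensus clustering, and by comparing equal with data-driven weights. Clusters are then described by their centroids and most important features.

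Table 1 lists many symptom and distress scales (ISI, FIRST, DBAS-16, MFI, PSAS, PHQ-9, GAD-7, PHQ-15, SF-MPQ-2 and others). It also lists wearable EEG, accelerometry, four cognitive tasks, chronotype and personality. The Results give a baseline ISI of 15.5 with SD 5.8.

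**The concern.** Scales of insomnia, fatigue, arousal, mood, anxiety, pain and somatic complaints tend to rise and fall together. Z-scoring each column leaves a person's general level in the data, and PCA gathers that shared variation into one high-variance component, which the 85% rule retains. K-means minimizes within-cluster squared distance, so it gains most by cutting along directions of high variance. If the general level outweighs the differences in pattern, the result is low, middle and high groups.

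The screen for near-duplicates at |r| > 0.8 does not touch this. Two scales that each load 0.4 on a common factor correlate at only 0.4 × 0.4 = 0.16, and at loading 0.5 the correlation is 0.25. The choice of k is not the cause either, since the effect appears at the true k.

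The stake is the main result. Severity bands may well predict follow-up ISI or depression, because baseline severity can itself be prognostic. They would add little to a severity score the study already holds, and groups that differ in kind at equal severity would be missed.

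**Working it through.** **The document's own figure.** The Study population section plans on this basis: "an estimated 40–80 variables will be included in the statistical model". It sets 50 events per variable, and 80 × 50 = 4,000 (40 × 50 = 2,000), which matches "a total of 4,000 participants are required at the baseline". The concern disputes no stated number. The 4,000 and the 40–80 variables serve below as inputs.

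**Assumptions not in the document.** Four equal-sized subtypes with the same mean severity; a share s of each loaded feature's variance due to one common severity factor (0 to 0.5); each subtype raised by d within-subtype SDs on its own quarter of the features.

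**Why bands can win.** With p features, m of them loading on severity:

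- Variance along the severity direction: L = m·s + (1 − s).
- Four bands along it capture about 0.87 of L (the simulated value for pure bands).
- Between-subtype variance per feature: ¼(0.75d)² + ¾(0.25d)² = 0.1875d². Over all features, B = 0.1875·p·d².

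Bands reduce the K-means criterion more than the true subtypes do when 0.87·L exceeds B. Mixed solutions appear before that point. Example with p = m = 80, s = 0.2, d = 0.8: L = 16 + 0.8 = 16.8, 0.87 × 16.8 = 14.6, and B = 0.1875 × 80 × 0.64 = 9.6.

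**Simulation 1.** N = 4,000, p = 80, Z-scores, PCA to 85%, K-means at k = 4. ARI is the adjusted Rand index against the true subtypes. The last column removes each person's mean over the severity-loaded features first.

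| m | s | d | 0.87·L | B | ARI, planned | Severity variance explained | ARI, adjusted |
|---|---|---|---|---|---|---|---|
| 80 | 0.1 | 0.8 | 7.7 | 9.6 | 0.44 | 0.48 | 0.97 |
| 80 | 0.2 | 0.8 | 14.6 | 9.6 | 0.16 | 0.75 | 0.98 |
| 80 | 0.3 | 0.8 | 21.5 | 9.6 | 0.00 | 0.86 | 0.99 |
| 80 | 0.1 | 1.2 | 7.7 | 21.6 | 1.00 | 0.00 | 1.00 |
| 80 | 0.4 | 1.2 | 28.4 | 21.6 | 0.17 | 0.77 | 1.00 |
| 40 | 0.1 | 0.8 | 4.3 | 9.6 | 0.97 | 0.00 | 0.97 |
| 40 | 0.2 | 0.8 | 7.7 | 9.6 | 0.43 | 0.49 | 0.97 |
| 40 | 0.4 | 0.8 | 14.4 | 9.6 | 0.15 | 0.76 | 0.99 |

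With no common severity factor (s = 0, d = 0.8) the planned sequence gives ARI 0.96.

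**Simulation 2.** N = 2,937 (recruited by June 2025), 40 self-report features loading 0.3, 0.4 or 0.5 on severity, 20 objective features loading weakly, k = 4. Figures are the percentage placed in the true subtype; random placement is about 25%. Separation is the distance of subtype means from the grand mean per feature (d = 0.8 above corresponds to √0.1875 × 0.8 = 0.35 SD).

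| Separation | Pipeline | 0.3 | 0.4 | 0.5 |
|---|---|---|---|---|
| 0.45 SD | no modality balancing | 99 | 74 | 67 |
| 0.45 SD | with modality balancing | 98 | 98 | 74 |
| 0.35 SD | no modality balancing (separate set of runs) | 90 | 62 | 43 |

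At 0.6 SD recovery was 90–100%. Residualizing on a broad severity score gave 91–100% across the 0.35–0.6 SD runs.

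**Do the planned checks catch it?** Data with a severity continuum and no subtypes at all gave bands with bootstrap ARI 0.95, 0.93 and 0.90 at k = 2, 3 and 4. Where true subtypes were present but missed, bootstrap ARI was lower (0.40–0.86), which signals some instability but not its cause. Consensus clustering was not simulated; it too measures repeatability. With severity mainly in questionnaire and EMA features (s = 0.3–0.4), three weighting schemes gave ARI 0.00–0.35 against the true subtypes.

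**The case against.** Four points on the other side carry weight.

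- The inputs that drive the result are assumed. The article gives no feature list, loadings or separations, and Table 1 holds many non-symptom measures. A reader might infer that the plan will return severity bands, or that harm starts at a fixed loading near 0.4. The document supports neither: at 0.6 SD separation the planned sequence recovers nearly everyone.
- The article does state a modality-balancing step, and it helps. At loading 0.4 and 0.45 SD it lifted recovery from 74% to 98%. Figures from runs without it do not describe the plan's own pipeline. At loading 0.5, however, recovery was still 74%.
- Centroid summaries would show ordered, parallel profiles, so bands need not pass unnoticed. That stands, but describing bands does not recover the subtypes that were missed.
- Severity may be a legitimate subtype axis. The Background itself cites a biologically more severe form as a prior subtype, so excluding severity by definition, or requiring a co-primary adjusted analysis, would go too far. Nor does the aim that the work "is anticipated to transcend unstable, symptom-based classifications" promise to remove severity: the Background uses the symptom-based label for types of night-time complaint.

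It can also be said that a condensed article leaves sensitivity analyses to the SAP, and that Longitudinal modeling allows methods to change. But this article does fix the clustering sequence and does name its sensitivity analyses, and none of them addresses severity. A general licence to adjust, used after the clusters are seen, is weaker than a stated check.

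**Conclusion.** The concern holds as a possibility that the plan should guard against, not as a certain failure. When many scales share a moderate severity factor and subtypes are modestly separated, the stated sequence can yield severity bands at the true k, and the planned robustness checks would not identify them as such. Across the assumed scenarios correct placement ran from about 40% to 100%. Modality balancing lessens the loss, and wide separation largely avoids it. The size rests on assumed loadings, four equal-severity subtypes and assumed separations; the study's own data will decide where it falls. Nothing in the article is misstated or contradictory here. The improvement is worth making because it bears on the primary outcome and is cheap.

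**What to change.** Keep the planned clustering as primary and pre-specify one sensitivity clustering:

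1. Before PCA, residualize each feature on a reliable severity score: a broad mean over the standardized symptom scales, or a general factor. Person-centring over severity-related features scored in the same direction is an alternative. A mean of only three scales can be too unreliable. At 0.35 SD it gave 94%, 92% and 74% correct at loadings 0.3, 0.4 and 0.5 when those scales loaded no higher than the rest, against 96–98% for the mean of all 40.
2. Report the ARI between the adjusted and planned solutions.
3. Report the share of severity-score variance that the planned clusters explain. For orientation, pure bands gave 0.63, 0.79 and 0.86 at k = 2, 3 and 4, and well-recovered equal-severity subtypes gave about 0.
4. State in advance what counts as a high share. If the share is high and the adjusted solution differs, describe the planned clusters as mainly severity levels.

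The cost is one more run on data already being collected, and a severity-driven solution must be reported as such. The article mixes past and future tense over these steps, so the addition should be dated and should say which clustering had already been run.
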